## Abstract

Background

Neonates, particularly if born preterm or with congenital anomalies, are among the pediatric patients most likely to need blood transfusion. However, they are also particularly vulnerable to adverse consequences of blood transfusion. Aiming to clamp the umbilical cord for at least a minute after birth is a simple safe procedure that is being increasingly adopted worldwide, although may be associated with increased rates of polycythemia and jaundice. It may also reduce the proportion of preterm babies who need a blood transfusion. The mechanisms for this are not fully understood. Potential mechanisms could include an increased volume of blood transfusion from the placenta to the baby after birth, and an overall reduction in the severity of illness in the first weeks after birth, which could lead to fewer blood tests and greater tolerance of anemia, or enhanced erythropoiesis.

Objectives

To investigate the mechanism behind the reduced need for blood transfusions after deferral of cord clamping.

Methodology

This protocol outlines the methods and data analysis plan for a study using nested retrospective data from a large randomized trial combined with additional data collected from patient medical and pathology records. The additional data items to be collected all relate to the receipt of transfusion and the factors that affect the risk for transfusion in preterm babies. The analysis will include all randomized babies from Australia and New Zealand for whom data are available. Causal mediation analysis is planned to estimate the effects of mediators on the relationship between the timing of cord clamping and the need for blood transfusion. The analysis is designed to discern whether initial severity of illness or the magnitude of placental transfusion mediates red blood cell transfusion dependence.

Anticipated outcomes and dissemination

We expect the study will identify potential strategies for reducing blood transfusions and associated negative outcomes in preterm infants. This will be relevant to researchers, clinicians, and parents. The results will be disseminated through publications, presentations, and inclusion in evidence-based guidelines.

## Introduction

Immediate cord clamping (ICC), within a few seconds after birth, became routine in the latter half of the 20th century, as part of a tranche of medical birth-related interventions that collectively, undoubtedly improved maternal and neonatal survival and outcomes [1]. The trend to ICC (within 15-20 seconds after birth) was partly driven by some early studies suggesting that the most benefit in terms of blood volume is achieved within this time frame [2], and that deferred cord clamping (DCC) increased rates of polycythemia and jaundice [1]. It may also have been partly driven by increased rates of operative deliveries and consequent pressure to minimize surgical times, as well as the increased availability and effectiveness of neonatal resuscitation. Furthermore, ICC was proposed as a means to reduce the risk of maternal exposure to fetal blood group antigens at a time (before RhD immunoprophylaxis) when hemolytic disease of the fetus and newborn was far more common than it is now.

Formal evidence that ICC was beneficial was never sought, and recent research summarized in systematic reviews [3-6] has suggested that it may be harmful when compared with DCC for various intervals from 30 seconds until when the cord stops pulsating (defined in some studies as physiological cord clamping). ICC before the onset of breathing exposes the newborn baby to a period of significantly restricted cardiac function, whereas DCC until after the onset of breathing (which often does not occur until late in the first minute after birth) may mean that the expanding pulmonary circulation is able to fill with blood from the placenta, rather than by reverse flow across the ductus arteriosus [7]. This may improve left ventricular preload and stabilize pressures and flows in major vessels [7].

In addition, when cord clamping is deferred, babies may receive a transfusion of blood from the umbilical cord and placenta. A recent systematic review demonstrated that DCC in preterm babies improves peak hematocrit in the first week by 2.7% (95% confidence intervals (CI) 1.88-3.52) and reduced the proportion of babies receiving any subsequent blood transfusion (RD: -0.07, 95%CI -0.11 to -0.04) [6]. Some studies have found a weight increase in the first two minutes after birth when the cord is not clamped, supporting the hypothesis of placental transfusion [8]. Yet, recent evidence shows that placental transfusion may not always occur (Conference abstract: Vijayaselvi R, Abraham A, Kumar M, Kuruvilla A, Mathews J, Duley L. Measuring Umbilical Flow and Placental Transfusion for Preterm Births: Weighing Babies at 33-36 Weeks Gestation with Cord Intact. 1st Congress of Joint European Neonatal Societies; 2015).

The relative roles of cardiovascular stabilization at birth versus placental transfusion in improving outcomes have not been established. Understanding the contributions of these two mechanisms has significant implications for research and practice: for example, if the size of placental transfusion is more important, then prescribing a top-up transfusion soon after birth for babies with lower than average hemoglobin (who are known to be at higher risk of various adverse outcomes) [9] may be justified, especially for the babies for whom DCC has been precluded by maternal or fetal conditions. These include significant maternal bleeding, and monochorionic twins, where deferred cord clamping in the first twin could lead to one twin losing blood to the other. However, if it is the effects on improving cardiovascular stability in the first minutes (with consequential benefits for cardiorespiratory function and reducing severity of illness during the subsequent neonatal intensive care unit (NICU) stay), regardless of the magnitude of transfusion, then early top-up transfusion is unlikely to be helpful.

Observational studies suggest that exposure to blood transfusion itself is harmful to preterm babies, increasing the risk of adverse outcomes [10]. However, this suggestion has not been supported by the small number (to date) of randomized controlled trials of blood (red cell) transfusion thresholds [11-14]. It is unlikely to be the means by which DCC reduced deaths in the largest trial to date of deferred cord clamping in preterm babies, the Australian Placental Transfusion Study (APTS), and in the most recent systematic review on this, because neither showed a difference in rates of other adverse outcomes [6,15].

Another possibility is that it is the umbilical cord blood stem cells received by the baby are the main reason for the observed benefits to both survival and reduced requirement for later blood transfusion [16]. Umbilical cord blood has been demonstrated to be such a good contributor to hematopoiesis that it is a recognized stem cell resource for pediatric and adult hematopoietic stem cell transplant [17]. In addition, umbilical cord blood is a potential regenerative and immunomodulatory agent for a variety of clinical conditions [18], so in this case, the extent of placental transfusion would be critical to the improvement of outcomes, and transfusion with adult red cells would not suffice. There are no established methods to quantify the contribution of umbilical cord stem cells to placental transfusion. However, a larger volume of placental transfusion results in the baby receiving more nucleated cells [19], including more umbilical cord stem cells.

Discerning whether these effects (initial enhanced cardiovascular stability leading to early and sustained reduction in severity of illness or volume of placental transfusion) appear to be the main driver of improved outcomes is likely to contribute to practice change, as well as to informing the design of future research studies into methods to improve outcomes of high-risk newborn babies and reduce their transfusion dependence.

The causal mechanisms of reduced transfusion requirements found in DCC relative to ICC are yet to be resolved. The aim of the study is to address the question; In preterm infants (P) does DCC (I) compared to ICC (C) reduce dependence on red cell transfusion via enhanced cardiovascular stability (mediator 1, M1) or via an increased volume of placental transfusion (M2).

## Materials and methods

Study design

The study is a nested retrospective study, called the Transfusions in the APTS Newborns Study (TITANS) (study registration: ACTRN12620000195954), of the cohort of babies who were enrolled and randomly assigned to ICC or DCC in the Australian and New Zealand (NZ) sites for APTS (study registration: ACTRN12610000633088). This design has been developed to take advantage of the comprehensive dataset already collected for APTS, and because there is currently no suitable prospective study that could address the same research questions in such a large group of participants.

Babies had been considered eligible for APTS if obstetricians or maternal-fetal medicine specialists anticipated that delivery would occur before 30 weeks of gestation. Exclusion criteria included fetal hemolytic disease, hydrops fetalis, twin-twin transfusion, genetic syndromes, and potentially lethal malformations. Further details are available in the original APTS publication [15]. In the present TITANS analysis, we will also exclude any baby with a diagnosis of hemolytic anemia or aplastic/hypoplastic anemia.

Recruitment and data collection

There were 1401 babies enrolled for APTS from the 13 Australian and 5 NZ hospital sites [15]. APTS data was provided to the TITANS team on 31 July, 2020. It is planned to collect additional data from Australian and NZ APTS sites using a customised, secure web-based database application (REDCap) [20], which is maintained by the University of Sydney, Sydney, Australia. Data will be obtained from source documents (patient hospital records and laboratory reports) using the electronic data collection application from each study site. The individual participant data collected will correspond to the minimum data required to answer the research questions. Baby identification (ID) and other babies’ details from APTS will be used to re-identify participants and link them to hospital records. Identified data will be collected, in order to allow linkage between the data newly collected from patient records and hospital laboratories and the existing APTS dataset. The data will be checked with respect to range, internal consistency, consistency with published reports and missing items. After data cleaning and analysis, data will be stored in re-identifiable form, with each participant’s data being identified with the same study numbering system as used for the APTS study.

Objectives

We will combine the data already extracted, stored and cleaned from APTS with the additional data obtained from study sites for each participating baby, to determine which factors are most influential in reducing transfusion requirements. The specific objectives are, after adjustment for prior risk factors (listed below), to determine:

1. Whether the effect of the intervention (cord clamping) on the outcome (blood transfusions) is mediated by placental transfusion (measured by hematocrit (Hct)) as seen in Figure 1 (a, c) following the causal path X → M1 → Y, where X is the intervention, ICC or DCC, Y is the outcome, mediator M1 is placental transfusion, and M2 is initial severity of illness stability

2. Whether the effect of the intervention (cord clamping) on the outcome (blood transfusions) is mediated by initial severity of illness (respiratory support, sampling line yes/no and total duration number, blood pressure, cumulative blood sample volume) as seen in Figure 1 (b, c) following the causal path X → M2 → Y

3. Whether the effect of cord clamping intervention on the outcome (blood transfusions) is driven by multiple mediators (placental transfusion and initial severity of illness) as seen in Figure 1 (c)

4. Whether cording clamping intervention (ICC or DCC) has a direct effect on the outcome after accounting for the mediators as seen in all panels of Figure 1: X → Y.

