The intervention consisted of either immediate or delayed cord clamping (as assigned in APTS). Immediate clamping was defined as clamping the cord within 10 seconds of delivery. Delayed clamping was defined as clamping the cord at least 60 seconds after delivery, with the infant held as low as possible, below the introitus or placenta, and with no palpation of the cord. Variations in the protocol were allowed if they would aid the mother, baby, or both. If the baby was non-vigorous (heart rate <100 beats per minute, low muscle tone, or lack of breathing, or crying), clinicians were allowed to break protocol using their discretion. Cord milking was not part of the protocol for either intervention. Further details may be sourced from the original APTS publication [15].

Outcomes

The primary outcome is the proportion of babies receiving red cell transfusion (for restoration of hemoglobin or blood volume). The secondary outcomes are number of transfusions per baby, cumulative transfusion volume (mL/kg) per baby, and primary reasons for each transfusion.

Putative Mediators

M1: Indicators of placental transfusion to be assessed will be hematocrit (on admission, highest on the first day, highest in the first week collected before any postnatal transfusion).

M2: Indicators of initial severity of illness to be assessed will be cumulative blood sample volume collected throughout hospital stay (number of blood tests multiplied by hospital’s usual sample volume for each type of test), sampling line (umbilical arterial line or peripheral arterial line) - yes/no and total duration, mechanical ventilation or inspired O2, and blood pressure.

Sensitivity Analyses (For the Primary Outcome Analysis Only)

Sensitivity analyses will adjust for the following variables: gender, birth <27 weeks vs. ≥27 weeks, method of delivery (vaginal versus cesarean), intraventricular hemorrhage (IVH) (yes/no and grade III/IV yes/no), surgery for patent ductus arteriosus (PDA), necrotizing enterocolitis (NEC), and sodium in the first 24 hours of life. We will also test model assumptions relating to sequential ignorability and post-randomization confounding (discussed further in the data analysis plan).

Potential Confounders (Covariates)

The following covariates may be used for adjustment in the analysis: gestational age at randomization before birth and any oral iron supplement pre-transfusion.

Timing of Assessments

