Putative mediating variables will only be analyzed if they have been measured before the outcome and will be excluded if there is not adequate time and date information available. If the multiple mediator model is applied, careful consideration of timing information will be evaluated. If there is insufficient empirical information to conclude the causal ordering of mediators (M1 causes M2), we will adjust our analytic approach (as discussed in the analysis plan) and discuss any limitations.

Data Analysis Plan

The analysis will include all babies who were initially randomized in the APTS trial for whom we were able to obtain the relevant data and be based on intention-to-treat. All statistical analyses will be conducted in R version 4.1.3 (2022-03-10; R Foundation for Statistical Computing, Vienna, Austria). Descriptive characteristics for continuous data will be presented as means or medians, as appropriate, and categorical data will be presented as frequencies and percentages.

A model-based inference approach will be applied to estimate the average causal mediation effect (ACME), average direct effect (ADE), and the average total effect as recommended [23-25]. This approach will be applied with the R “mediation” package [26]. We will initially fit two models, one model with mediation as the dependent variable and intervention as the independent variable (mediator model), and a second model with the outcome as the dependent variable, and both mediation and intervention as independent variables (outcome model). To account for the clustering of multiples, estimates will be calculated with generalized estimating equations with a compound symmetric correlation structure to account for within subject correlations. Depending on the outcome (binary, count, skew) these will be modelled with the appropriate family and link functions.

A counterfactual framework will be applied to the mediator and outcome models to simulate the values of the mediator and outcome to estimate the potential values of the mediator. This process is used to estimate the ACME, ADE, and average total effects; 95%CI will be estimated with 1000 bootstrap simulations.

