3.5	ICC / DCC	remaining Hct variables*	Blood pressure	Transfusions any/vol/n

Sensitivity analyses have been limited to a set of biologically plausible and clinically meaningful groups that will be explored by including them for adjustment with covariates, and with the introduction of interaction terms if appropriate. Missing data will be described, reasons for missing data will be explored, and the impact of missing data on conclusions about the treatment effect on the primary outcome will also be explored where possible (e.g., using sensitivity analyses and multiple imputation techniques).

Methodological Assumptions

The causal mediation approach assumes sequential ignorability: that the treatment effect on the outcome is not confounding and that the mediator effect on the outcome is not confounded. As treatment was randomly allocated to neonates, we will assume that the treatment-mediator relationship is not confounded. However, the mediator itself has not been randomized. Thus, unknown confounders may be driving a spurious effect in the mediator-outcome relationship. We will employ additional sensitivity analyses to estimate whether any mediation effects are sensitive to the violation of the assumption of sequential ignorability. To test the possibility of unmeasured confounders we will examine the correlation between residuals in the mediator model and the outcome model. If there is no correlation this would suggest there is no unmeasured confounding, if there is correlation between the residuals, an unmeasured mediator may be affecting both the measured mediator and the outcome. We will apply the method developed by Imai et al. and Tingley et al. [23,26] that uses sensitivity analyses to evaluate if the ACME estimate is sensitive to unmeasured confounding.

Post-randomization confounders are dependent on the treatment allocated, affect both mediator and outcome, and can corrupt the mediation estimate. In the context of the present trial, it is possible that non-adherence to the intervention is a post-randomization confounder. We are analyzing our data based on intention to treat principles; however, a sensitivity analysis based on the actual time of cord clamping to assess the influence of non-adherence with the treatment protocol on our estimates may be performed.

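### The TITANS exclusion of babies with hemolytic or aplastic/hypoplastic anemia is applied after randomisation, is not limited to conditions present before birth, and conflicts with the stated intention-to-treat population

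*Protocol article*

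**What the plan says.** Study design first lists what kept babies out of the parent trial: "Exclusion criteria included fetal hemolytic disease, hydrops fetalis, twin-twin transfusion, genetic syndromes, and potentially lethal malformations". It then adds a further rule for the present study: "In the present TITANS analysis, we will also exclude any baby with a diagnosis of hemolytic anemia or aplastic/hypoplastic anemia". The wording covers any such diagnosis and does not tie it to a condition that existed before birth or before the cord was clamped.

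The new information comes from existing records (Recruitment and data collection): "Data will be obtained from source documents (patient hospital records and laboratory reports) using the electronic data collection application from each study site".

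Three other places describe the population or the principle of analysis, and none mentions the added exclusion:

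- Abstract, Methodology: "The analysis will include all randomized babies from Australia and New Zealand for whom data are available".
- Data Analysis Plan, opening sentence: "The analysis will include all babies who were initially randomized in the APTS trial for whom we were able to obtain the relevant data". The same sentence adds that the analysis rests on intention to treat.
- Methodological Assumptions: "We are analyzing our data based on intention to treat principles".

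The outcome is defined under Outcomes: "The primary outcome is the proportion of babies receiving red cell transfusion (for restoration of hemoglobin or blood volume").

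**The concern.** A randomised comparison is protected as long as membership of the analysis set cannot depend on anything that happened after allocation. The parent trial's exclusions were entry criteria. The added exclusion is different: it acts on babies who have already been allocated and treated, through a diagnosis read from the chart.

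The diagnoses concerned are forms of anemia, and the primary outcome is transfusion of red cells. As worded, the rule also catches a label given during the investigation of the anemia that led to a transfusion, or after it. The section on timing of assessments requires mediators to precede the outcome, but no matching condition is attached to this exclusion.

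If the chance of receiving such a label differed between the arms, the remaining groups would no longer be the groups that were randomised. Methodological Assumptions uses random allocation as the ground for treating the intervention-to-mediator path as unconfounded, and warns that treatment-dependent events after randomisation can distort mediation estimates. The total effect, the indirect effect and the direct effect would all be exposed.

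**Working it through.** **1. Consistency of the text.** Take a randomised Australian baby with complete data and a postnatal chart diagnosis of hemolytic anemia. Under Study design the baby is out. Under the Abstract and the Data Analysis Plan the baby is in, because the only limit stated there is whether data could be obtained, and they were. This conflict needs no assumption about bias.

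**2. Size of a possible bias in the total effect.** The article gives no number excluded and no transfusion risk per arm, so there is no figure of its own to reproduce. What follows is an illustration.

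Inputs:
- Assumed transfusion risk: 60% with immediate and 50% with deferred clamping, a difference of -10.0 points. The Discussion reports a reduction of about 10% without saying whether it is absolute or relative; this takes it as absolute.
- Assumed fraction excluded, e, and fraction of those who were transfused, t.
- 1401 babies (Recruitment and data collection), or about 700 per arm if allocation was 1:1 (assumed).

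Risk after exclusion = (p - e × t) / (1 - e).

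| Assumed exclusion | Immediate | Deferred | Difference |
|---|---|---|---|
| 1% in each arm, all transfused | (0.60 - 0.01)/0.99 = 0.596 | (0.50 - 0.01)/0.99 = 0.495 | -10.1 points |
| 2% immediate, 3% deferred, 90% transfused | (0.60 - 0.018)/0.98 = 0.594 | (0.50 - 0.027)/0.97 = 0.488 | -10.6 points |
| 4% immediate, 2% deferred, all transfused | (0.60 - 0.04)/0.96 = 0.583 | (0.50 - 0.02)/0.98 = 0.490 | -9.4 points |
| Rows 2 and 3 together | (0.60 - 0.058)/0.94 = 0.577 | (0.50 - 0.047)/0.95 = 0.477 | -10.0 points |

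**3. A harsher case.** Use the risk difference of -0.07 from the systematic review cited in the Introduction, an assumed 50% risk with immediate clamping, and exclusion of 2% in one arm only, all transfused:
- Deferred arm only: (0.43 - 0.02)/0.98 - 0.50 = -0.082.
- Immediate arm only: 0.43 - (0.50 - 0.02)/0.98 = -0.060.

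Over assumed immediate-arm risks of 50% to 70% and differences of -7 or -10 points, this one-sided case shifts the result by about 0.6 to 1.2 points. Equal exclusion of 0.5% to 2% per arm shifts it by at most 0.2 points.

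**4. Scale.** The standard error of the risk difference at 60% and 50%, ignoring the clustering of multiples, is √[(0.60 × 0.40 + 0.50 × 0.50)/700.5] = 0.026, or 2.6 points. A shift of 0.6 points is about a quarter of that; 1.2 points is just under half.

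**5. What this leaves out.** The calculation covers only the total effect. It says nothing about the size of any bias in the average causal mediation effect or the average direct effect.

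**The case against.** The best defence is that the rule extends the parent trial's own exclusions, some of the same kind, and is meant for babies with intrinsic red cell disease whose transfusions have nothing to do with cord clamping. If those conditions precede birth and are found equally well in both arms, the rule narrows the target population with little or no bias. In a study of mechanism that is a defensible choice. This stands as a reading of intent, but the sentence as written is not restricted that way.

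It can also be said that the Data Analysis Plan is shorthand: it omits the restriction to Australia and New Zealand too, and it already depends on obtainable data, so it never promised a complete intention-to-treat set. That is fair, and it makes the conflict easy to repair. It does not remove it, because a baby with full data is not excluded by a data-availability clause. Diagnostic definitions and time windows may sit in the full protocol or analysis plan; their absence from an article is no fault and is not charged here.

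Two stronger readings are tempting and not supported:

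- A reader might infer that these diagnoses are known to be affected by clamping. No section says so. The Abstract says only that deferral is a procedure "although may be associated with increased rates of polycythemia and jaundice"; going from jaundice to a hemolysis work-up to more exclusions after deferral is inference. So is the idea that enhanced erythropoiesis would make a hypoplastic label rarer. Erythropoiesis is background here; the mediators tested are hematocrit and initial severity of illness.
- A reader might infer that the rule selects on the outcome. It selects on a diagnosis that may follow from anemia or from transfusion, not on transfusion itself.

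**Conclusion.** The point holds as a conflict within the article and as a possible, unproven selection bias. The exclusion acts after randomisation and treatment, its wording reaches beyond conditions present before birth, and it does not fit a population of all randomised babies with data analysed by intention to treat.

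The likely effect on the total effect is small: about 0.1 to 0.6 points on an assumed -10 with assumed exclusions of 1% to 4%, in either direction, and near zero when the two unequal scenarios are combined. Anything material needs exclusions that differ clearly by arm, which the article neither shows nor rules out. All exclusion rates and arm risks used are assumptions, as is 1:1 allocation. The claim that the results will be biased would go too far. The change is justified because it is cheap and restores the stated population.

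**What to change.** Reconcile the Abstract, Study design, Data Analysis Plan and Methodological Assumptions so that they define one population. Either of two forms would do:

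- Keep every randomised Australian and New Zealand baby with data in the primary analysis, whatever the later diagnosis.
- Keep an exclusion, but restrict it to conditions present before birth, ascertained without knowledge of arm and transfusion status, and name it in each description of the population.

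In either case, report the number of babies with these diagnoses, and the number excluded, by arm, and give the analysis excluding all such diagnoses as a sensitivity analysis.

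Under the first form the cost is mainly wording: a few babies transfused because of unrelated red cell disease stay in and add slight noise. The second form adds the work of blinded ascertainment. Figure 2 leaves the study's numbers to be filled in once data collection is complete, so the change can be made before the analysis set is fixed.

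### The stated aim is to rank two mechanisms, but every planned estimate has its own interval and none compares the mechanisms

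*Protocol article*

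**What the plan says.** Mediator numbering here follows the Objectives and Table 1: M1 is placental transfusion, measured by hematocrit (Hct), and M2 is initial severity of illness.

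**The aim.** The Objectives section says the data will be combined "to determine which factors are most influential in reducing transfusion requirements". The Abstract puts it as one or the other: "The analysis is designed to discern whether initial severity of illness or the magnitude of placental transfusion mediates red blood cell transfusion dependence". The Introduction says that discerning which effects "appear to be the main driver of improved outcomes is likely to contribute to practice change". It attaches different practice implications to the answer. One branch begins "if the size of placental transfusion is more important, then prescribing a top-up transfusion soon after birth for babies with lower than average hemoglobin". The other applies if cardiovascular stability is what matters "regardless of the magnitude of transfusion, then early top-up transfusion is unlikely to be helpful".

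**The analysis.** The Data Analysis Plan will "estimate the average causal mediation effect (ACME), average direct effect (ADE), and the average total effect as recommended", and "95%CI will be estimated with 1000 bootstrap simulations". If M1 and M2 are independent, models 1.0 to 1.2 and 2.0 to 2.4 in Table 1 are fitted one mediator at a time. If not, models 3.0 to 3.5 take both mediators and again yield an ACME and an ADE with intervals. The fallback yields path-specific effects. The Results section promises the total and indirect effects with 95% CIs, plus the exposure-mediator and mediator-outcome estimates. The four numbered objectives each ask whether an effect exists.

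**The concern.** Whether each mechanism operates and which one matters more are different questions. Separate intervals answer the first. The second needs an estimate of the difference between the two indirect effects, with its uncertainty, and none is planned.

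Without it, a reader who wants the ranking that the article promises must set one interval against another. This is unsafe because each ACME is a product of two paths, and the two products can have very different precision at the same true size. Two equally important mechanisms can then look like one driver and one non-driver. The single-mediator models may also rest on different babies, since the footnote to Table 1 allows that not enough babies may have both mediators measured.

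**Working it through.** The article gives no sample size or power figure for the mediation effects, so there is none to reproduce. The check has a textual part and an illustration.

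**Text.** The Data Analysis Plan, Table 1, the Results section and the fallback method contain no difference, ratio or contrast between the M1 and M2 effects, no rule for naming the more influential one, and no size below which an effect counts as negligible.

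**Inputs from the article.** At most 1401 babies (Recruitment and data collection); Hct shift of 2.7 points and risk difference of -0.07 for any transfusion (Introduction).

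**Assumptions.** Baseline transfusion risk 60%; 1:1 allocation; M1 and M2 independent given treatment; no clustering; no missing data. An Hct SD of 8 to 10 points gives a shift of 2.7/8 = 0.34 to 2.7/10 = 0.27 SD; a shift of 0.40 SD would need an SD of 2.7/0.40 = 6.75. The severity shift is taken as 0.10 to 0.20 SD.

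**Step 1: context.** Power for the whole effect, 700 per arm, 60% against 53%: SE = √[(0.60×0.40 + 0.53×0.47)/700] = 0.0264; z = 0.07/0.0264 = 2.65; power = Φ(2.65 − 1.96) ≈ 75%. Each mediated part is smaller than the whole.

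**Step 2: general rule.** Two equal effects, estimated independently with power p each, give exactly one significant result with probability 2p(1−p): 50% at p = 0.5, 32% at 0.8, 18% at 0.9.

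**Step 3: why precision differs.** The treatment-to-mediator path, in SD units, has SE ≈ 2/√1401 = 0.0534. That path alone caps the power of the ACME.

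| Severity shift (SD) | z | Approximate cap on power |
|---|---|---|
| 0.10 | 1.87 | 46% |
| 0.15 | 2.81 | 80% |
| 0.20 | 3.75 | 96% |

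For Hct, a shift of 0.34 SD gives z = 6.4, so its limit is the mediator-to-outcome path. With an ACME of -1.5 points and a shift of 0.40 SD, that path is 0.015/0.40 = 0.0375 per SD; its SE ≈ √0.24/√1401 = 0.0131, z = 2.9, power about 82%.

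**Step 4: simulation.** Both ACMEs truly equal, total effect -7 points, N = 1401, 2000 data sets per row, simulation-based 95% intervals.

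| Hct shift | Severity shift | Each ACME (points) | Only Hct CI excludes 0 | Only severity CI excludes 0 | Contrast CI excludes 0 |
|---|---|---|---|---|---|
| 0.34 | 0.10 | -2.0 | 52.0% | 0.0% | 5.0% |
| 0.34 | 0.15 | -2.0 | 21.7% | 0.1% | 4.8% |
| 0.34 | 0.20 | -2.0 | 3.0% | 0.5% | 4.9% |
| 0.40 | 0.15 | -1.5 | 16.1% | 14.0% | 4.2% |
| 0.40 | 0.20 | -1.5 | 3.4% | 17.0% | 5.0% |

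Over all 18 combinations run (Hct 0.30, 0.34, 0.40; severity 0.10, 0.15, 0.20; ACME -1.5, -2.0), discordance ran from 3.5% to 55.2% and false positives of the contrast from 3.7% to 5.8%. A separate run with both shifts at 0.10 SD and ACMEs of -2 points gave 24.5% + 26.1% = 50.6% discordance, split evenly. With 1000 babies and severity shifts of 0.10 to 0.15 SD, discordance was 36% to 64%.

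**Step 5: power of the contrast.** For a true twofold difference (-3.0 against -1.5 points, shifts 0.40 and 0.15 SD), the contrast CI excluded zero in 43% of data sets when Hct had the larger effect and in 23% when severity had it.

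**The case against.** The best defence is that the numbered objectives do match the analysis. Each asks whether, each has an estimate, and the third allows both mechanisms to act. The Results section reports sizes and intervals that a careful reader can weigh. A contrast from existing bootstrap draws might also sit in a fuller analysis plan. This is right about the numbered objectives. It does not remove the mismatch, because the sentence introducing them and the Abstract both promise a comparison, and the article sets out its own estimands, model table and reporting without one.

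Three stronger readings are tempting, and the article does not support them:

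- **That the plan will dismiss a mediator whose interval includes zero.** No such rule, significance level or p-value criterion is stated.
- **That the error leans towards placental transfusion.** This needs a small severity shift. The Introduction's remark that other adverse outcomes did not differ says nothing direct about ventilation, sampling lines, blood pressure or blood sampling. The last two rows of the simulation table show that the imbalance can vanish or reverse.
- **That a conclusion about top-up transfusion would rest on poor precision.** That sentence is a conditional in the Introduction about the true mechanism, not an analysis rule. Its severity branch would need Hct to be missed and severity found, which occurred in about 1% of data sets with shifts of 0.40 and 0.10 SD and ACMEs of -2 points.

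A simple difference also has limits. Table 1 allows 3 × 5 = 15 pairs of indicators, and if M1 influences M2 the pathways share a segment. Both limits are met in the fix.

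**Conclusion.** The point holds as a mismatch between a comparative aim and a set of non-comparative estimates. The planned ACMEs, direct effects and intervals are not made invalid by it; what lacks support is the step from them to a ranking.

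The size is uncertain. With equal true effects, discordant intervals appear in about half of trials if the severity shift is 0.10 SD, mostly 16% to 33% at 0.15 SD, and often below 10% at 0.20 SD. A direct contrast stays near its nominal 5% throughout. Baseline risk, Hct SD, severity shift and independence of the mediators are assumptions. The figures therefore show that the error is plausible, not how often it would occur here, and no direction should be claimed. The point merits a change before analysis.

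**What to change.** In the Data Analysis Plan, for the primary outcome:

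1. Name one pair of indicators in advance, for example peak Hct with one severity indicator from models 3.0 to 3.2.
2. Estimate both indirect effects on the risk-difference scale in the same babies and the same bootstrap resamples, drawing mothers so that multiples stay together. Report the difference with its 95% CI as the sole basis for any statement about the most influential factor or main driver.
3. If M1 and M2 are causally linked, contrast the path-specific effects and state to which mechanism the shared path is assigned.
4. State that an interval including zero is not evidence that a mechanism is absent, and that an inconclusive contrast means the ranking is unresolved.

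If the team does not want the contrast, the alternative is to reword the aim so that it no longer promises a ranking.

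The computing cost is small: one further quantity from a joint bootstrap, and a few sentences. The real costs are that the contrast is confined to babies with both mediators measured, and that its power is limited (about 40% or less for a true twofold difference under the assumptions above). An unresolved ranking will be a common and honest result.
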